### Study sample

We aim to include *N* = 42 schools to ensure there is enough power for the analyses (*N* = 21 schools for both the intervention and waitlist control condition). This sample size is sufficient to examine the effectiveness of Meaningful Roles and potential moderators, with a power of 0.80, an alpha of 0.05 and a medium effect size of 0.21 [18].

Participants are children from the upper grades of primary school (grades 5–8) in the Netherlands, their teachers (who will implement the program) and school leaders. The children will mostly be between 8 and 12 years old.

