#### Moderators

*Child, teacher, and school characteristics* will be collected at baseline. Child characteristics include age, gender, romantic attraction (i.e., possibility of falling in love with a boy/girl), grade, and ethnic identity. Teacher characteristics include age, gender, years of experience (as a teacher in general, and as a teacher at the specific school) and experience with implementing social safety programs, as well as attitudes of the teachers. School characteristics include location, number of participating grades and students in the classrooms, and years of experience with a social safety program (e.g., KiVa).

*Working elements* will be assessed halfway through the program (T2) and after completion of the program (T3), with specific questions developed for this study. Children and teachers fill in questionnaires related to the three main components of the program: 1) meaningful roles (e.g., “How much did you like the role(s)”, “Which roles were the most popular?”, respectively), 2) classroom meetings (e.g., “The weekly meetings were done independently by the class”, “How often has a meeting been held?”, respectively), and 3) compliments (e.g., “I have received compliments from my classmates”, “How many times a week has attention been paid to the compliments?”, respectively). Higher scores reflect a more positive or greater adherence of the working elements.

*Program integrity* will be assessed halfway through the program and after completion of the program, with specific questions developed for this study. Teachers and school leaders fill in (open and closed) questionnaires related to the implementation of the program, divided into the domains training and material (e.g., “How often have you used the manual?”), child questionnaires (e.g., “Where there any questions that the children struggled with?”), time investment (e.g., “How did you feel about the time you had to implement the program properly?”), and global impression (e.g., “What is your general impression of the degree of success of the implementation of the program?”). Higher scores reflect a more positive or greater adherence of the program.

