### Statistical analyses

Before the analyses, possible baseline (T1) differences in demographics and outcome variables (baseline assessment) between children in the intervention program and the control condition will be checked with ANOVA (continuous variables) and chi-square analyses (categorical variables). To investigate the effectiveness of the intervention program, regression analyses will be performed. The dependent variables are the outcome measures at intermediate (T2) or posttest (T3), condition is the predictor variable (1 = intervention, 0 = control), and baseline (T1), potential differences between the experimental and control group at T1, or intermediate measures (when dependent variables are the outcome measures at T2) are the covariates. The effect of potential moderators (categorial or continuous) on the outcomes will be examined by adding interaction effects to the models.

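### One power claim (42 schools, 0.80, effect 0.21) is made for both the main effect and the moderators; if it holds for the main effect, a two-category school-level moderator has power of only about 0.29

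*Protocol article*

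**What the plan says.** The protocol article, Study sample, sets the size at the school level: "We aim to include *N* = 42 schools to ensure there is enough power for the analyses", with "21 schools for both the intervention and waitlist control condition". It then makes one claim for two kinds of analysis: "This sample size is sufficient to examine the effectiveness of Meaningful Roles and potential moderators, with a power of 0.80, an alpha of 0.05". The effect size in the same sentence is 0.21. It has no stated metric, and the text does not say whether it is a main effect or an interaction.

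The Design section randomises schools 1:1. Statistical analyses tests moderators, categorical or continuous, by adding interactions to the regression models. The Moderators section names those measured on schools: "School characteristics include location, number of participating grades and students in the classrooms, and years of experience with a social safety program". Current study makes the examination of moderators the second aim.

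**The concern.** A test of whether a program works differently in two groups of schools is less precise than a test of whether it works at all, because it compares two treatment effects, each estimated from part of the schools. One sample size therefore cannot have the same power for a main effect of 0.21 and for a difference of 0.21 between two groups of schools. The sentence reads as if it did.

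The second aim is at stake. If a real difference of 0.21 between, say, urban and nonurban schools has power 0.29, it would be missed in about 71% of such trials (1 − 0.288 = 0.712). The published sample-size statement would still suggest that the search had power 0.80.

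**Working it through.** **Inputs from the protocol article.** 42 schools, 21 per arm, randomised 1:1; power 0.80; alpha 0.05; effect size 0.21; moderators tested as interactions.

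**Assumptions.** Two-sided test; 0.21 is a standardised mean difference; the interaction is as large as the main effect (0.21); the moderator has two categories, spread alike over the arms.

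**Step 1: the plan's own figure.** It can be neither confirmed nor refuted, because it depends on children per school, ICC and the gain from T1 adjustment. An article may leave these to a fuller document. I therefore grant the claim for the main effect and ask what follows.

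**Step 2: standard error implied by power 0.80.**
- Normal approximation: 1.960 + 0.842 = 2.802, so SE = 0.21 / 2.802 = 0.0750.
- Noncentral t, 40 df: noncentrality 2.871, so SE = 0.21 / 2.871 = 0.0731 and the variance is 0.00535.

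**Step 3: standard error of the interaction.** With a share p of schools in one category, SE(interaction) = SE(main) / √(p(1 − p)).
- p = 0.5: √0.25 = 0.5, so the SE doubles and the variance is four times as large.
- p = 0.25: √0.1875 = 0.433, so the variance is 1 / 0.1875 = 5.33 times as large.

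The variance of a school mean, which carries the ICC, the school size and any T1 gain, is a common factor of both SEs and cancels from the ratio.

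**Step 4: power for an interaction of 0.21.** Power = Φ(2.802 × √(p(1 − p)) − 1.960).

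| Split of schools | Normal | Noncentral t, 38 df | Detectable at power 0.80 (normal) |
|---|---|---|---|
| 50/50 | Φ(−0.559) = 0.288 | 0.288 | 0.21 / 0.5 = 0.42 |
| 25/75 | Φ(−0.747) = 0.228 | 0.228 | 0.21 / 0.433 = 0.485 |

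At an even split, power 0.80 for an interaction of 0.21 would take about 4 × 42 = 168 schools. This shows the scale of the gap; it is not a proposal. A one-sided alpha of 0.05 would raise 0.288 only to 0.34.

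**Step 5: the reverse.** If the evenly split interaction had power 0.80, main-effect power would be Φ(2 × 2.802 − 1.960) = Φ(3.643) = 0.9999. With 42 schools and m children per school, the interaction variance is 4 × (2/21) × (ICC + (1 − ICC)/m), multiplied by the share of variance that T1 leaves unexplained (taken as equal at both levels). Power 0.80 requires ICC + (1 − ICC)/m ≤ 0.0140 without T1 adjustment. At an assumed m = 80 this gives:
- no T1 gain: ICC ≤ (0.0140 − 0.0125) / 0.9875 = 0.0015;
- T1 explains 50%: ICC ≤ (0.0280 − 0.0125) / 0.9875 = 0.016;
- T1 explains 70%: ICC ≤ (0.0467 − 0.0125) / 0.9875 = 0.035.

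**Step 6: where the result does not carry over.**
- Continuous school-level moderator: per SD of the moderator, the interaction has about the same SE as the main effect, so 0.21 per SD has power of about 0.80.
- Child-level moderator, split evenly within schools: power depends on school size. With no T1 gain, no variation of its effect between schools, and the ICC that gives the main effect 0.80, it is about 0.41 at 25 children per school and 0.94 at 100. T1 adjustment would change these figures.
- Teacher-level moderator: it also depends on class-level clustering, on which the article gives nothing.

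**The case against.** A reader might infer that 42 schools cannot give power 0.80 for both kinds of test under any circumstances, or that every school-level moderator has power 0.29. The document supports neither.

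- *Sufficient* may mean at least 0.80. The fourfold variance ratio is fixed, but whether both tests pass 0.80 is not: Step 5 gives ICCs at which they do. This stands, and it rules out calling the claim impossible. It also means that the main effect would then be far overpowered at 0.21, and nothing in the article says that this was intended.
- Most of the listed school characteristics are counts or years, and for a continuous moderator at 0.21 per SD the claim survives. This stands too. However, 0.21 per SD is the larger interaction: an evenly split two-category moderator has an SD of 0.5, so 0.21 per SD corresponds to 0.42 between its two groups. Location is naturally categorical; the Background contrasts urban with nonurban settings.
- A reader might also fault the article for giving no ICC, children per school or T1 correlation, for calling 0.21 medium, or for applying one alpha to many outcomes. The first is detail that an article may leave out. The second depends on an unstated metric and changes no analysis. The third is a separate matter. None of them is part of this point.
- Nothing in the article says that a non-significant moderator will be read as equal effectiveness. Current study expects unequal effects, and the Discussion says only that a large sample could allow moderators to be examined. The harm is thus a risk of misreading, not a planned misuse.

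What remains is a stated power that does not follow for a type of moderator the protocol names.

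**Conclusion.** The concern holds in limited form, as something that should be fixed. The single claim of 0.80 cannot be carried from the main effect to a categorical school-level moderator. If main-effect power is 0.80 at 0.21, power for an interaction of the same size is about 0.29 at an even split and 0.23 at 25/75, and the detectable interaction is about 0.42, twice the stated effect. This rests on a two-sided test, a two-category moderator balanced over the arms, and 0.21 read as a standardised difference that applies to both tests. It does not rest on any ICC or school size. The main-effect figure itself is not shown to be wrong, and no conclusion is drawn on child- or teacher-level moderators beyond their dependence on inputs that the article does not give.

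**What to change.** Reword the sample-size statement in Study sample:

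1. Claim power 0.80 at an effect of 0.21 for the main effect of condition only.
2. State separately the smallest interaction detectable with power 0.80: about 0.42 for a two-category school-level moderator at an even split (about 0.485 at 25/75). Give the corresponding values for teacher- and child-level moderators on the trial's own assumptions about school size, clustering and T1 correlation.
3. Label moderator analyses that do not reach power 0.80 as exploratory, and report them as interaction estimates with confidence intervals.

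The cost is a few sentences and a less favourable stated power for part of the second aim. No extra schools, data or changes to the analysis model are needed.

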### Recruitment

Primary schools will be approached in person, via email and/or via telephone (mainly based on contacts of the intervention and research team). If schools show interest in participating in the Dutch adaptation of Meaningful Roles, they will receive (written) information about the project and what participation entails. Schools are also invited to an online orientation meeting. In this meeting the intervention and research team will clarify information about the program and research study, as well as answer questions from schools. If schools agree to participate, they will sign a cooperation form and will be randomized into the intervention or waitlist control condition. Parents/caregivers of children will be informed about the project (via mail, information evenings, telephone) by schools and will be asked to give active informed consent for participation of their child in the study (on paper or digital). Children aged 12 years or older will be asked for active informed consent themselves before they start the online questionnaire, in addition to their parents/caregivers. All children will be notified that participation is voluntary and that they can stop at any moment. Teachers and school leaders will be asked for active informed consent for their own participation in the study via a digital consent form, right before they start the online questionnaire. Children without permission/consent do not receive the research questionnaire, but they do receive the Meaningful Roles program.

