## Methods

### Design

A cluster RCT will be conducted. Schools will be randomized (stratified for number of participating classrooms) into the intervention condition in which the program starts immediately or into a control condition that receives the program one school year later (see Fig. 2), using an online randomization tool [33] in a 1:1 ratio. We will recruit a diverse sample of children from primary schools in the Netherlands.

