### Data collection

Online questionnaires assessing demographics (e.g., age, gender), primary outcomes (i.e., prosocial behavior, intrinsic prosocial motivation, social competence, social autonomy, and social relatedness) and secondary outcomes (i.e., school wellbeing, social position, and antisocial behavior) will be completed by children prior to the start (T1) of the program. Halfway through the program (T2) and after completion of the program in the intervention condition (T3), children complete questionnaires about program content (i.e., working elements) in addition to questionnaires assessing primary and secondary outcomes. Teachers complete questionnaires about demographics (e.g., age, years of experience), attitudes, and civic skills at T1 and questionnaires about attitudes, civic skills, program content (to assess program integrity), and program evaluation at T2 and T3. Additionally, one teacher from each school will participate in the focus groups (at T1, T2, and T3), to evaluate the implementation of the program (i.e., qualitative information). Table 1 presents an overview of the instruments at each assessment point.

**Table 1 Tab1:** Overview of the variables’ instruments and sources

Outcome	Variable name	Instrument	Time of measurement	Variable type	Source
Primary outcomes					
Prosocial behavior	Injunctive norm	Developed for this study	T1, T2, T3	Outcome	Child
	Prosocial behavior (individual)	Based on the Strengths and Difficulties questionnaire (SDQ), subscale prosocial behavior	T1, T2, T3	Outcome	Child
	Prosocial behavior (according to classmates)	Sociometric nominations	T1, T2, T3	Outcome	Child
	Cooperation in the classroom	Classroom Peer Context Questionnaire (CPCQ), subscale cooperation	T1, T2, T3	Outcome	Child
	Conflict in the classroom	Classroom Peer Context Questionnaire (CPCQ), subscale conflict	T1, T2, T3	Outcome	Child
Intrinsic (prosocial) motivation	Social goals	Developed for this study	T1, T2, T3	Outcome	Child
Social competence	Self-esteem	Developed for this study, based on de Rosenberg Self-Esteem Scale	T1, T2, T3	Outcome	Child
Social autonomy	Social autonomy and responsibility	Developed for this study, based on the School as a Caring Community Profile – II and Child Development Project [34]	T1, T2, T3	Outcome	Child
Social relatedness	Comfort and cohesion	Classroom Peer Context Questionnaire (CPCQ), subscale comfort and cohesion	T1, T2, T3	Outcome	Child
Secondary outcomes					

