### Dutch Meaningful Roles program

The Dutch adaptation of Meaningful Roles is a classroom-based program implemented by teachers. Teachers receive two three-hour training sessions from trained and experienced educational professionals. Meaningful Roles is an approach (throughout the schoolyear) for primary school groups 5 to 8 (children between 8–12 years old). The aim of Meaningful Roles is to improve the classroom climate and mutual relationships in the group, in a positive, prosocial way.

The program consists of three main components: meaningful roles, classroom meetings, and compliments (see Fig. 1 for the conceptual model). With regard to the roles, children are given specific roles to actively work on autonomy and responsibility, competence, and prosocial behavior. These roles, such as newsreader or plant caretaker, are prosocial in nature, because children help one or more children or are considerate of other children in the class. Moreover, roles give children autonomy and responsibility, as the children are free to perform the role as they see fit. The roles are aimed to optimize the strengths and talents of each child, through giving children the experience that they can contribute something that increases their confidence in their own abilities. During the weekly classroom meetings, children take the leading role in discussions about the classroom functioning and agreements: they discuss how they feel and what the atmosphere is like in the classroom. This ensures interaction and connection with each other and stimulates children’s feeling of competence, autonomy and responsibility in social classroom processes. Last, children learn how to give and receive effective compliments and practice with doing so on a structural basis, which strengthens trust in others and reinforces confidence in one’s own abilities.

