## Discussion

This study protocol presents the design of a cluster RCT to investigate the effectiveness of a classroom-based program, Meaningful Roles, to promote a more prosocial classroom climate in primary schools, through improving intrinsic motivation to behave prosocial, by enhancing SDT components (i.e., social autonomy, social competence, and social relatedness). This is important, because a positive, prosocial classroom climate is associated with an optimal learning environment, as well as positive school quality and wellbeing in children [1, 2]. Previous research showed improved prosocial classroom climate (e.g., increased prosocial behavior) in youth after receiving school- or classroom-based social-emotional focused programs (e.g., [11, 15]), as well as improved psychological health after receiving programs focused on STD components [22]. To overcome limitations of previous research, including suboptimal study design (e.g., non-randomization) and target group (e.g., US samples), we will examine a classroom-based approach for upper primary school students and use a cluster RCT to exclude confounding (e.g., allocation and selection bias) as much as possible. We will use a multi-informant (i.e., child, teacher, school leader) and multi-method (i.e., questionnaires and focus groups) approach. Moreover, we strive to use a large, diverse sample, that could allow us to examine potential moderators of program effectiveness (i.e., child, teacher, school, and program characteristics, i.e., working elements and program integrity).

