There are several challenges in this study, such as the recruitment of a sufficient number of schools (and students) and the collaboration with multiple parties. First, it may be difficult to recruit sufficient schools with a diverse and representative sample of students and maintain the involvement of schools, teachers, students, and parents over the course of the study. Recruitment of schools may be difficult because we would preferably like schools to participate with all their upper classes (groups 5–8), which requires involvement and participation of multiple teachers (who all need to stand behind the program and research). To recruit schools, we will mainly try to contact schools who already have connections or collaborations with the research or implementation team (i.e., KiVa schools), making the first contact easier. These schools are located all throughout the Netherlands. As such, it is likely that diverse schools, with a diverse sample of students, will be represented in our study. Additionally, flyers will be distributed via mail and newsletters, and information meetings will be organized to give more information about the program and study participation.

Second, since participation of students requires active informed consent from their parents, it is crucial that all parents of participating classes are reached and are provided with clear information about study participation. Participating schools make sure that parents receive information about the project, and teachers will be responsible for contacting parents (e.g., face-to-face, mail, telephone). In order to make giving permission as easy as possible, parents can also give digital consent. Researchers and the contact person of the schools will be in constant contact to increase response rates. These precautions are expected to increase the likelihood of participation of students.

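### Schools are described as randomised on signing, before teachers seek parental consent and with T1 tied only to program start, so protection from selection bias is not secured at child level

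*Protocol article*

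**What the plan says.** - **Randomisation (Recruitment):** "If schools agree to participate, they will sign a cooperation form and will be randomized into the intervention or waitlist control condition".
- **Parental consent (Recruitment):** the next step described is that schools inform parents, who "will be asked to give active informed consent for participation of their child in the study". Children without consent get no research questionnaire, so consent defines the analysed sample.
- **Teacher and school-leader consent (Recruitment):** given digitally, immediately before their own questionnaire.
- **Who pursues parental consent (Discussion):** "teachers will be responsible for contacting parents (e.g., face-to-face, mail, telephone".
- **Who delivers the program (Dutch Meaningful Roles program):** it "is a classroom-based program implemented by teachers".
- **What the allocation means (Design):** schools are randomised "into the intervention condition in which the program starts immediately or into a control condition that receives the program one school year later". The Control condition section adds that control schools get no materials or training in the meantime.
- **Timing of T1 (Data collection):** the children's questionnaires "will be completed by children prior to the start (T1) of the program".
- **Analysis (Statistical analyses):** T1 differences are checked, and baseline and differing variables enter the regressions as covariates.
- **Claim (Discussion):** the authors will "use a cluster RCT to exclude confounding (e.g., allocation and selection bias) as much as possible".

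**The concern.** In a cluster trial, randomising schools balances schools. It balances the children analysed only if they enter the sample independently of the allocation. Here the described order puts the draw first, and the people seeking consent are the teachers who will, or will not yet, be running the program. The two arms are easy to tell apart: one has training and an immediate start, the other has a year's wait.

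If consent rates differ by arm, or if different kinds of families consent in each arm, the analysed children are no longer comparable by design. Baseline adjustment then has to do what randomisation was meant to do, and it can do so only for what T1 measures. T1 may itself be answered after the arm is known. Adding schools does not help, because a shift of this kind does not shrink with sample size.

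**Working it through.** **Order of steps.** Set side by side, Recruitment ties the draw to the school's signature and then describes parental consent. Data collection fixes T1 relative to program start only. None of the sections on design, recruitment or data collection says that the result is held back until consent or T1 is complete. Nothing described makes entry of children independent of arm.

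**Inputs.** The plan gives no consent rates and no figure on this point. Its only relevant number is the effect size of 0.21 (Study sample), used here as a yardstick. All consent figures below are assumptions.

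**Calculation 1: extra consenters.** Let c1 and c0 be the consent proportions in the intervention and control arms. Let d be the difference in baseline mean, in SD, between the extra families who consent only under the more successful recruitment and those who would consent in either arm.

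Shift in arm means = (c1 − c0)/c1 × d

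| c1 v c0 | d | Shift (SD) | Share of 0.21 |
|---|---|---|---|
| 80% v 75% | 0.5 | 0.05/0.80 × 0.5 = 0.031 | 15% |
| 80% v 70% | 0.5 | 0.10/0.80 × 0.5 = 0.0625 | 30% |
| 80% v 70% | 1.0 | 0.10/0.80 × 1.0 = 0.125 | 60% |

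**Calculation 2: graded selection.** Let a baseline trait X be standard normal and the probability of consent be 1/(1 + exp(−(a + bX))), with a chosen to give the stated rate. The mean of X among consenters is E[pX]/E[p]. The table gives the absolute difference between arms.

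| Consent | Slope b, intervention / control | Difference (SD) | Share of 0.21 |
|---|---|---|---|
| 80% v 80% | equal | 0 | 0% |
| 80% v 70% | 0.3 / 0.3 | 0.029 | 14% |
| 80% v 70% | 0.5 / 0.5 | 0.047 | 22% |
| 80% v 60% | 0.3 / 0.3 to 0.5 / 0.5 | 0.058 to 0.093 | 28 to 44% |
| 80% v 80% | 0 / 0.3 to 0 / 0.5 | 0.059 to 0.096 | 28 to 46% |
| 80% v 60% | 0 / 0.3 to 0 / 0.5 | 0.118 to 0.189 | 56 to 90% |

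**Reconciling the two at 80% v 70%.** Dividing the second model's results by 0.10/0.80 = 0.125 gives the d it implies: 0.029/0.125 = 0.23 and 0.047/0.125 = 0.38. The first calculation assumed 0.5 to 1.0. The methods agree; they differ only in how unlike the others the extra consenters are taken to be. With the same selection process in both arms, the range is therefore about 0.03 to 0.13 SD.

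**Reading the results.** The direction is not determined: it depends on which families are added or missing. Equal consent rates alone are not reassuring, since the 80% v 80% row with unequal slopes is not zero. All values are before T1 adjustment. The documents give no correlation between T1 and later scores, so no adjusted figure is offered.

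**The case against.** **The order is read from the narrative.** Recruitment proceeds party by party and gives no dates, the flow chart is not available here, and stratifying by number of participating classrooms would be compatible with a later batch draw. This stands as a caveat. Even so, the text links randomisation to signing and describes nothing that conceals the result.

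**The mechanism is not documented.** Nothing says that waitlist teachers would try less hard or that parents are told the arm. Refusing consent does not cost a child the program. Digital consent, constant contact with schools and weekly recruitment updates are described without distinction by arm. This is fair: the point is a risk, not an observed bias.

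**Stronger readings that the documents do not support.**
- A reader might infer that protection from selection bias is lost altogether. It is not: school-level protection remains, and the Discussion's claim is itself qualified.
- A reader might take 30 to 60% of the target effect as the expected bias. Those shares need extra consenters who differ by 0.5 to 1.0 SD, which nothing in the article supports, and they ignore T1 adjustment.
- A reader might infer that teachers collect the children's T1. The article says only that children complete online questionnaires.
- A reader might infer that allocation distorts T1 throughout. Age, gender, grade or years of experience would not change with knowledge of the arm; only the self-reported attitudes and behaviours could.
- A reader might infer a mechanical gap in peer-nomination scores. The divisor is given as the number of classmates, but the article does not say how non-consenting classmates are counted.

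**Conclusion.** The point holds as a weakness of the described sequence. As written, children, and teachers through their own consent, enter the sample after their school has been randomised, with no described concealment. The protection claimed in the Discussion is therefore not secured at child level, and covariate adjustment recovers only the part that T1 captures.

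The size cannot be known from the document. At assumed consent of 80% v 70% and the same selection process in both arms, the unadjusted shift is about 0.03 to 0.13 SD. It would be larger with wider gaps or arm-specific selection, and zero if consent and selection are equal. This should be changed because the remedy is cheap, not because bias has been shown. The planned number of schools is not affected.

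**What to change.** State and follow this order: the school signs the cooperation form; parental consent closes; the class list is fixed; children and teachers complete T1; only then is the allocation drawn or released and training scheduled. With consent closed before release, consent cannot depend on arm, and the expected selection difference is zero.

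This reorders existing steps and needs no more schools. Its cost is shorter notice for intervention schools to arrange the two training sessions, which matters for a program meant to run through the school year.

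Where a school must know its arm earlier:
- use one parent letter that is neutral as to allocation;
- report consent rates and T1 characteristics by arm, since equal rates alone do not rule out different selection;
- qualify the Discussion's statement, so that it claims protection against selection of schools and not of children.

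If consent and T1 were already planned before release of the allocation, one clarifying sentence in Recruitment is enough.
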